### 2.1 Primary target variables

1. Physical activity: The primary outcome measure is the achieved Metabolic Equivalent (MET)-minute count per week in strenuous and moderate activity. This will be compared to WHO guidelines on health-promoting physical activity (600 MET minutes per week). In addition, the average sitting time in hours per day will be quantified. These primary outcome measures will be examined for gender and faculty differences and target groups with below-average physical inactivity and high sedentary behavior identified.

2. Nutrition: The main target variable is the summed value of all 10 identified food categories summarized as the Healthy Eating Index of the National Eating Survey II (HEI-NVS II index). This indicates whether the DGE recommendations of healthy eating are met (≥ 100 points). These primary outcome measures will also–as all following target variables—be examined with respect to gender and faculty differences to identify target groups with a higher-than-average unhealthy eating pattern. Thus, target groups with above-average unhealthy eating behavior can be detected.

3. Relaxation and stress reduction: The primary outcome measure is stress experience as measured by the summed score of the Perceived Stress Scale-10(PSS-10). This will be applied to examine how many students have a moderate to high stress experience (PSS-10 sum > 13). The 5 coping strategies of the Stress and Coping Inventory (SCI) represent another outcome measure of the primary objective. They are each assigned to a below-average or above-average performance level in order to determine target groups with above-average stress experience.

4. Self-management: The main target variable is the self-management competence of the students, measured by the sum value of the SMST. It examines the number of students who have mediocre to very poor self-management skills (SMST sum score < 13). As such, the identification of target groups with below-average self-management skills is made possible.

5. Psychosocial health, consisting of a) alcohol and drug use, b) depression, c) anxiety disorders, and d) sleep disorders:

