## 3. Study population

### 3.1 Inclusion and exclusion criteria

Only students from the 11 faculties of the ALU Freiburg are allowed to participate in the needs analysis. For this purpose, the following inclusion and exclusion criteria have been defined:

Inclusion criteria:

Enrolled at the ALU Freiburg≥18 years of age

Exclusion criteria:

Institutes or universities that do not belong to ALU Freiburg (private institutes, university of education, universities of other sponsors in Freiburg, etc.).Employees of the ALUDoctoral studentsStudents with physical impairments that prevent them from moderate and/or strenuous physical activity.Students with an impairment/illness that strongly influences their dietary behaviorStudents who have a severe psychological impairment

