## 5. Biometry

The present study is an exploratory study conducted monocentrically and prospectively at ALU Freiburg in Germany. Based on the 2014 German Student Survey on sample selection and representativeness of data, a sample of > 500 students is recommended to obtain a sufficiently large number of students in the different subject distributions [37]. Approximately 0.9% of all students at the universities took part in a survey in the winter semester 2012/13. Participation varied between the universities by 0.6–1.6%. It was pointed out that for representative statements, it is not so much the relative proportion of the sample to the population that is important, but the absolute size of the sample. With this in mind, > 500 students are expected to participate in the survey in the present investigation, thus creating a representative sample.

Data analysis will be conducted using IBM SPSS Statistics version 26.0. All tests are two-sided and the significance level will be set at α = 5%. Effect size d will be calculated according to Cohen (1988) and interpreted as follows: < 0.2 (no effect); ≥ 0.2 (small effect); ≥ 0.5 (moderate effect); and ≥ 0.8 (large effect) [65]. To test the data for normal distribution, if necessary, the Shapiro-Wilk test will be chosen due to the large sample size.

In principle, the data collected on prevalence in relation to exercise, nutrition, relaxation and stress reduction, self-management, psychosocial health, and sociodemographic data of students of the ALU Freiburg will be illustrated and presented by means of descriptive statistics and graphs, since this is primarily a description of the opportunity sample. Therefore, the number of the sample population is given as N and as a percentage. For interval-scaled data, the mean (MW) and ± standard deviation (SD) will also reported. Along with the MW and SD, the median will also be given for the descriptive analysis of the parameters.

In order to investigate whether the national and international guidelines are met by students in the respective areas, a Chi-square test will be performed by a cross-tabulation. At the same time, the cross-tabulations will also be used to compare the respective faculties. Using a t-test for independent samples, differences in characteristic expressions, such as gender and faculty differences, will be analyzed. If there is no normal distribution, the Mann-Whitney U-test will be applied.

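### Faculty differences in scores are assigned a two-group test although there are 11 faculties, so chance differences are likely to be among those that inform target groups

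*Protocol article*

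**What the plan says.** Section 5 (Biometry) of the protocol article names the test for group differences in scores: "Using a t-test for independent samples, differences in characteristic expressions, such as gender and faculty differences, will be analyzed". The alternative follows at once: "If there is no normal distribution, the Mann-Whitney U-test will be applied". The error level is general: "All tests are two-sided and the significance level will be set at α = 5" per cent. No multi-group test of scores is named.

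Section 3.1 gives the number of groups: "Only students from the 11 faculties of the ALU Freiburg are allowed to participate in the needs analysis". Section 3.2 repeats the figure of 11.

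For categorical guideline status, section 5 plans Chi-square tests on cross-tabulations and adds: "At the same time, the cross-tabulations will also be used to compare the respective faculties".

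Section 2.1 gives the purpose, first for physical activity: "These primary outcome measures will be examined for gender and faculty differences and target groups with below-average physical inactivity and high sedentary behavior identified". Under nutrition, the gender and faculty comparison is extended to the other domains ("as all following target variables"). Section 2.2 extends it to the secondary outcomes, and the Discussion links the information on student groups to tailored programmes.

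**The concern.** Gender, as counted in section 3.2, has two levels, so a two-sample test suits it. Faculty has 11, and neither named test can answer in one step whether faculties differ on a score. An analyst following the text must break the question into many two-group tests, each at 5%. The natural choices are every pair of faculties or each faculty against all others. Either way the error rate for the question actually asked, per outcome, is far above 5%.

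Faculty comparison is one of the stated uses of nearly every primary variable. Its results are meant to help decide which groups of students receive tailored offers. Spurious faculty contrasts would therefore be likely to enter that decision alongside real ones.

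**Working it through.** **Inputs from the article.** 11 faculties (sections 3.1 and 3.2); two-sided 5% for all tests (section 5); 24,391 students, more than 2% per faculty and more than 500 in total (section 3.2).

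**The plan's own figure.** 0.02 × 24,391 = 487.8, and 500 / 24,391 = 2.05%. The target of more than 500 is consistent with the 2% rule. The article gives no power or error-rate figure for faculty comparisons, so there is none to reproduce.

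**Number of tests per outcome.**
- All pairs: 11 × 10 / 2 = 55.
- Each faculty against the rest: 11.

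**Expected false positives per outcome if all faculties are equal.**
- 55 × 0.05 = 2.75.
- 11 × 0.05 = 0.55.

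**Chance of at least one false positive per outcome.** Pairwise tests share groups and are correlated, so the independence formula 1 − 0.95^55 = 0.94 is too high. The studentized range suits this case better. With N = 500, the degrees of freedom are 500 − 11 = 489 and the 97.5% t quantile is 1.965. The critical range is 1.965 × √2 = 2.779, and the upper tail for 11 groups is 0.674.

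Simulation with N = 500 and no true difference gave the table below. Equal means 45 or 46 students per faculty. Unequal is an assumed split from 8 to 110 students, because the article does not give faculty sizes.

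| Procedure | Equal sizes | Unequal sizes |
|---|---|---|
| 55 pairwise t-tests | 0.67 to 0.68 | 0.66 |
| 11 faculty-versus-rest t-tests | 0.42 | 0.42 to 0.43 |
| One-way ANOVA | 0.05 | 0.05 |

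For 55 Mann-Whitney tests on skewed data with equal sizes, the rate was 0.68; one Kruskal-Wallis test gave 0.045. For 11 tests the independence formula gives 1 − 0.95^11 = 0.43, close to the simulated value.

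**Across outcomes.** Section 2.1 yields about 15 primary scores: MET-minutes, sitting time, HEI, PSS-10, five SCI strategies, SMST, AUDIT, DUDIT, PHQ-9, GAD-7 and ISI. Adding the CSSQ would make 16.
- All pairs: 15 × 55 = 825 tests, and 825 × 0.05 = 41.25 expected false positives.
- Faculty against rest: 15 × 11 = 165 tests, and 165 × 0.05 = 8.25.

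Correlation between scores does not change these expected counts. A single multi-group test per score would still leave 1 − 0.95^15 = 0.54 for at least one false positive over 15 independent scores. The results across outcomes therefore need to be labelled exploratory even after the fix.

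**The case against.** The strongest reply has four parts.

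**The Chi-square tests already compare faculties.** This stands. A faculty-by-status table can test all 11 at once, and nine of the 15 scores carry a stated cut-off (MET-minutes, HEI, PSS-10, SMST, AUDIT, DUDIT, PHQ-9, GAD-7, ISI). A reader might infer that the plan has no joint test of faculties at all; the documents do not support that. The misfit is confined to comparisons on the score scale. Multiple regression could also handle a factor with many levels, and section 4.2.6 lists faculty among the sociodemographic data. However, section 5 presents regression as an addition to the difference tests and does not say how faculty would enter.

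**The 55 pairs are not in the text.** Correct. A reader might take all-pairs testing as planned, but the article is silent on pairing. Both readings are therefore shown; the milder one is still more than eight times the nominal 5%.

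**No rule says that a significant p-value selects a target group.** Also correct. Section 2.1 speaks of groups above or below average. A reader might infer that chance differences will be selected, but the text supports only that they are likely to be among the differences that inform the choice. The figures also assume that no faculty differs, whereas the Introduction and Discussion expect real variation between faculties.

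**The study is exploratory and mainly descriptive.** This weakens any complaint about missing multiplicity adjustment, which a full protocol or analysis plan could supply. It does not excuse a two-group test named for an 11-level factor, which is stated here and not merely left out.

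**Conclusion.** Wrong as written, and should be fixed. For outcomes analysed as scores, the article fixes a test that does not fit a factor with 11 levels. If faculties truly do not differ, at least one false faculty difference per outcome has a probability of about 0.41 to 0.43 (each against the rest) or about 0.67 (all pairs), instead of 0.05.

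These sizes rest on N = 500, unadjusted testing at 5% and no true differences. They change little between the equal and the assumed unequal faculty sizes. The totals of about 8 or 41 also rest on the count of 15 scores.

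The point does not touch the prevalence estimates, the guideline comparisons by Chi-square or the two-sample test for gender. Because this is an exploratory survey that is repeated every two years, with measures open to adjustment, the defect does not undermine the study as a whole.

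**What to change.** Reword the test paragraph in section 5:
- Keep the t-test or Mann-Whitney U-test for gender.
- For faculty differences in scores, name one multi-group test per outcome: Welch ANOVA, or Kruskal-Wallis for the rank-based analysis.
- Follow it with adjusted contrasts. For all pairs, use Games-Howell, or Dunn's test with Holm adjustment. If the question is which faculties depart from the university as a whole, use Holm-adjusted contrasts of each faculty against the overall mean. Games-Howell is an all-pairs method and does not serve that second purpose.
- When naming target groups, report faculty estimates with intervals and do not rely only on a position above or below average. Some faculties will lie on the unfavourable side even if all are equal.
- Label faculty results across outcomes as exploratory. False discovery rate control across outcomes and shrunken estimates from a random-intercept model are optional.

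The change needs no new data. It costs a few sentences and a little more analysis, and fewer faculty contrasts will be called significant.

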### 4.2 Questionnaire survey

At the start of the study and subsequently at two-year intervals until 2026, situation and needs analyses will be conducted using validated and evaluated questionnaires. Data will be collected via an anonymous and self-administered online questionnaire via Social Science Survey [SoSci Survey] [38]. All questionnaires applied have been validated and have already been employed in various studies addressing comparable issues. No modifications have been made to the questionnaires in the context of the present investigations that would necessitate a re-validation.

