#### 4.2.2 Nutrition

The German Health Examination Survey (DEGS) food frequency questionnaire for national health and nutrition monitoring is used to survey dietary behavior [42]. This consumption frequency questionnaire (FFQ) will be applied to collect the consumption frequency and usual portion amounts of a total of 53 foods consumed in the last four weeks. To assess food choices, dietary patterns will be based on the Healthy Eating Index of the National Eating Survey II (HEI-NVS II) [43]. Here, the 53 food items are divided into food categories, which are compared and evaluated on the basis of the recommendations of the German Nutrition Society (DGE) [44]. In accordance with Hilger et al. (2017), 22 items will be provided to determine which barriers prevent an unhealthy diet [45].

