In addition to highlighting differences, the sociodemographic variables will be examined together with other independent variables from the respective categories in a multiple regression. Spearman-Rho correlation or person correlation in the case of normal distribution will be used to check whether there are correlations between the study parameters.

Furthermore, to understand if there are causal relationships between the variables investigated, “Structural Equation Modeling” and the creation of causal models will be performed. Fig 1 shows the path diagram representing the theoretical associations between the latent and observed variables.

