**Fig 1 pone.0295166.g001:**
[figure not shown]
Structural equation modelling (SEM) path diagram of potential associations between the latent variables and their corresponding observed variables. Sociodemographic data: Age, BMI, Gender, Migration background. Nutrition; DEGS-FFQ: German Health Examination Survey; HEI: Healthy Eating Index of the National Eating Survey II. General Health State: HRQL-4: Health related quality of life. Psychosocial Health: GAD-7: Generalized Anxiety Disorder Scale; PHQ-9: Patient Health Questionnaire; ISI: German validated Insomnia Severity Index; DUDIT: Drug Use Disorders Identification Test; AUDIT: Alcohol Use Disorders Identification Test; COVID-19 Student Stress Questionnaire (CSSQ). Physical Activity: IPAQ: International Physical Activity Questionnaire; WST: weekly sitting time.

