## 6. Data management and data protection

Data management will be carried out in accordance with Good Clinical Practice (GCP) requirements and the provisions of the European Union Data Protection Regulation (EU-DSGVO). The data for the study evaluation will be collected per student via an online questionnaire using SoSci Survey. Large-scale scientific survey projects using SoSci Survey have been successfully conducted for the realization of such studies for many years. After data collection, SoSci Survey exports the data correctly, completely and immediately in the form of a spreadsheet to a password-protected computer and automatically deletes it irrevocably from the SoSci Survey server after 3 months. No one except the study director and the participating researchers (page 1) are allowed to view the password-protected and encrypted spreadsheet.

All student-relevant study data will be stored anonymously. Name, private address, personalized e-mail address, matriculation number or other identification numbers of students will not be requested. Merely a random number will be assigned to each student. Only after the students have voluntarily sent their number to the scientists involved (e-mail: [contact]), will it be possible to assign the person at great expense in terms of time, cost and manpower.

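### Structural equation models are planned to find out whether causal relationships exist, which a repeated cross-sectional, anonymous survey without described person-level linkage cannot show

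*Protocol article*

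**What the plan says.** In section 5 of the protocol article, the last analysis listed is structural equation modelling. Its stated purpose is "to understand if there are causal relationships between the variables investigated", and the sentence ends by saying that "the creation of causal models will be performed". The next sentence points to Fig 1 and describes its content as theoretical associations. The Fig 1 caption speaks of potential associations between latent variables and their observed variables.

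The same section calls the study exploratory and prospective, and describes the main output as a description of an opportunity sample.

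On data collection, section 4.2 says "Data will be collected via an anonymous and self-administered online questionnaire", and that "subsequently at two-year intervals until 2026, situation and needs analyses will be conducted". Section 6 says "All student-relevant study data will be stored anonymously". It adds that no identification numbers are requested and that "Merely a random number will be assigned to each student".

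On the model blocks, the Fig 1 caption lists "Sociodemographic data: Age, BMI, Gender, Migration background", and names both the DEGS food frequency questionnaire and the HEI under nutrition. Section 4.2.2 says of the index: "Here, the 53 food items are divided into food categories", which are then scored against the national recommendations.

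**The concern.** The stated purpose is to learn whether causal relationships exist. That requires information on direction and on common causes, which the described design does not supply. Activity, diet, stress and symptoms are answered in one questionnaire by self-selected respondents. No exposure is assigned, and no identifying assumption is stated.

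What is at stake is what the study may conclude. If a path from activity to depression fits well and is reported as a cause, the reverse path or a shared cause may explain the same data equally well. The article intends its findings to inform health measures, so the status of such a statement matters even in an exploratory analysis.

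A smaller question concerns the measurement side of the model. Age, BMI, gender and migration background are not natural reflections of one underlying factor. An index scored from a questionnaire is also not a second, independent indicator beside that questionnaire.

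**Working it through.** **Planning figure.** The only planning figure is the sample size. Section 3.2 gives 24,391 students and a target above 2% per faculty: 0.02 × 24,391 = 487.8, consistent with the stated total above 500 (500 / 24,391 = 2.05%). There is no power calculation to reproduce, and the causal point does not depend on sample size.

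**Step 1: what one record contains.**
- Diet covers the last four weeks (4.2.2).
- Stress covers the last month (4.2.3).
- Depression covers the previous two weeks, and insomnia the last month (4.2.5).

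These windows overlap and are all answered at one sitting, so no exposure is measured before an outcome by design.

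**Step 2: whether the waves add time order.** The survey is repeated every two years (4.2). With anonymous storage and only a random number per student (section 6), no route is described for joining one student's answers from different waves. Section 6 does say that a student can be identified after voluntarily sending in the number, but it does not present this as a linkage plan. As described, the design is repeated cross-sectional, with one occasion per analysable record.

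**Step 3: what model fit can show.** Take three standardised variables and two paths a and b.
- X→M→Y implies corr(X,Y) = a × b.
- Y→M→X implies corr(X,Y) = b × a.
- X←M→Y implies corr(X,Y) = a × b.

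With a = b = 0.4, each gives 0.4 × 0.4 = 0.16. Each model uses 2 paths and 3 variances (5 parameters) against 3 variances and 3 covariances (6 moments), so each has 6 − 5 = 1 degree of freedom and imposes the same restriction.

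Fitted by maximum likelihood to one simulated data set (n = 500 and paths of 0.4, both assumed), the results were:

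| Model | Chi-square |
|---|---|
| X→M→Y | 6.30e-06 |
| Y→M→X | 6.30e-06 |
| X←M→Y | 6.30e-06 |

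The chi-square is n times a discrepancy that is the same for all three, so they stay tied at any n. With only two constructs, X→Y, Y→X and a plain correlation each reproduce the single correlation exactly.

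**Step 4: internal consistency.** Section 5 describes the study as exploratory and mainly descriptive. The sentence after the causal claim, and the Fig 1 caption, speak only of associations. The causal clause stands alone against these.

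**Step 5: measurement blocks.** Sections 4.2.2 and the Fig 1 caption together show that the HEI is scored from the same 53 food items that make up the questionnaire listed beside it. The diagram is not available, so the caption alone does not show whether these are two indicators or an instrument and its score. Nor does it show whether the sociodemographic items are reflective indicators, formative indicators or plain covariates.

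**The case against.** The strongest reply is that the article already tempers the phrase: the study is labelled exploratory, and the figure is said to show theoretical or potential associations. This is also the last-listed analysis, and no target variable in section 2 is a path coefficient. All of that is true and limits the weight of the point. It does not remove it, because the purpose is stated in explicit causal terms and the surrounding text contradicts it.

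A second reply is that the equivalence example is narrow. The two chains and the fork belong to one equivalence class, and a collider (X→M←Y) would generally fit differently. Nor has it been shown that the full model in Fig 1 has an equivalent reversal. This stands. The example supports only the general statement that fit alone does not establish causation.

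Several stronger readings are tempting, but the document does not support them:
- **That the survey is one-time.** It is repeated until 2026. What is missing is a described linkage between waves.
- **That the listed indicators are invalid in general.** Section 4.2 states that the questionnaires are validated and unmodified, and nothing counts against GAD-7, PHQ-9, ISI or the other instruments. That statement covers the instruments and not the structure of the latent model, so a question remains for two blocks only.
- **That path coefficients will be used to choose health measures.** Section 2 derives the need for measures from the primary and secondary goals and does not mention this analysis.
- **That a latent sociodemographic factor would hide gender or migration effects.** Gender and faculty differences are tested directly, and sociodemographic variables enter a separate multiple regression.

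**Conclusion.** The causal aim in section 5 is wrong as written for the design described. This rests on two readings of the article: that exposures and outcomes come from the same sitting, and that no within-person linkage or identifying assumption is planned. If the full protocol describes either of the latter, the point would need to be reconsidered.

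The size cannot be put as a bias or a loss of power. It is a limit on what may be concluded: for equivalent models, the data carry no information on direction at any sample size. The descriptive results, guideline comparisons and group tests are untouched. The point therefore deserves correction but does not threaten the study.

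The measurement question is secondary and conditional on the diagram. It is a request to check two blocks, not a demonstrated error.

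**What to change.** **Main change.** In section 5, replace the causal purpose with the estimation of associations compatible with a pre-specified, hypothesised path model. Remove the references to causal relationships and causal models, and state that direction and causation cannot be inferred from these data. The cost is a few words and a weaker claimed conclusion. No data collection changes.

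**Conditional on Fig 1.**
- If age, BMI, gender and migration background are drawn as reflective indicators of one latent factor, enter them as separate observed variables.
- If the DEGS questionnaire and the HEI are both indicators of nutrition, keep only one.
- If the diagram already does this, a clarifying phrase in the caption is enough.

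The cost is at most a redrawn diagram and a respecified model.
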